### Data management {19}

Clinical data will be collected and managed using an electronic database during participants’ hospital visits at baseline, 2 months, and 4 months (Table 1). The paper version materials, which include the protocol, case reported forms, informed consent forms, and electronic version database, will be kept in an independently secured box at Shanghai Sixth People’s Hospital by the principal investigator. The research assistants will send out reminder emails and make phone calls to ensure that participants complete the research. If (1) the participant withdraws his or her consent and (2) exclusion criteria are discovered after registration, the participant will be removed from the study. The reason for the suspension as well as the date of the suspension will be documented. The consent form will include permission to utilize data collected prior to the participant’s withdrawal.

### Confidentiality {27}

All personal data of registered participants will be assigned a unique identifier and stored on a secure server available only to researchers with administrative privileges. After the trial, only non-personal data will be available for analysis in the data repository.

## Plans for collection, laboratory evaluation, and storage of biological specimens for genetic or molecular analysis in this trial/future use {33}

Not applicable; no biological specimens will be collected.

## Statistical methods

### Statistical methods for primary and secondary outcomes {20a}

SPSS 26.0 will be used for the statistical analysis. Continuous variables will be represented by a mean and standard deviation, whereas categorical variables will be represented by counts and percentages. The intention-to-treat principle will be used to analyze the UPDRS III score (primary outcome) [37], which will include data from all randomized individuals. A per-protocol analysis of other outcomes from the participants who completed the entire research will also be performed. Multiple imputations will be used to replace missing data using multivariable regression models with chained equations. The mean treatment differences and 95% CIs between measures with LIPUS and sham-LIPUS will be computed. All statistical tests will be two-sided with a *p* < 0.05 statistical significance level.

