### Criteria for discontinuing or modifying allocated interventions {11b}

In this study, the criteria for discontinuing the intervention will be (1) participants who are unable to complete the clinical study, (2) participants who voluntarily withdrew informed consent, and (3) participants who experience serious adverse events. As of now, no adverse events have been reported during the course of LIPUS treatment.

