### Plans to promote participant retention and complete follow-up {18b}

Patients will be required to participate in all evaluations and treatments over the course of the 4-month trial. The patients will be provided with trial-related assessments, such as rating scales and medical examinations, which will include ultrasound examinations, hdEEG, and fMRI, without incurring any financial expenses or burdens.

If a participant chooses to discontinue their involvement in the study during the therapy phase and fails to complete the entire 4-month treatment duration, their data will not be maintained for the purpose of analysis. It is imperative to exert all conceivable efforts in order to incentivize and provide assistance to patients, ensuring their sustained participation in the study until the completion of their intended outcome assessments.

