### Adverse events reporting and harms {22}

From the start of the trial (either LIPUS or sham treatment) to the 4-month follow-up visit, the primary safety endpoint is the occurrence of adverse events. The primary outcome is a four-month safety visit. Meanwhile, research visits will be scheduled every two months. Adverse events will be assessed using the following criteria: those reported spontaneously by participants, those reported in response to a particular inquiry for adverse events, and those noticed by the neurologists during the general and neurological examinations at each visit. All adverse events that occur throughout the trial will be meticulously documented.

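### Read as written, the completer rule in {20a} and the data-exclusion rule in {18b} can remove participants who leave early from the primary safety result

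*Protocol article*

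**What the plan says.** Five sections of the protocol article bear on who enters the safety result.

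- **Analysis set for UPDRS III, {20a}:** "The intention-to-treat principle will be used to analyze the UPDRS III score (primary outcome) [37], which will include data from all randomized individuals".
- **Analysis set for the rest, {20a}:** "A per-protocol analysis of other outcomes from the participants who completed the entire research will also be performed". No other set is named for these outcomes.
- **Early leavers, {18b}:** if a participant chooses to stop during the therapy phase and "fails to complete the entire 4-month treatment duration, their data will not be maintained for the purpose of analysis". Safety data are not excepted.
- **Data before withdrawal, {19}:** "The consent form will include permission to utilize data collected prior to the participant’s withdrawal".
- **Ending the intervention, {11b}:** the third listed criterion is "3) participants who experience serious adverse events".
- **Safety endpoint, {22}:** from the start of LIPUS or sham treatment "to the 4-month follow-up visit, the primary safety endpoint is the occurrence of adverse events". The same section adds: "All adverse events that occur throughout the trial will be meticulously documented". It names no analysis set.

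The Abstract also calls safety an outcome and places its primary assessment at 4 months.

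**The concern.** A safety result should count harm in everyone exposed to the device. Two stated rules here make inclusion depend on staying to the end: the completer set for other outcomes in {20a} and the removal of early leavers' data in {18b}. Harm is one of the main reasons why people leave a device trial. If the participants who are harmed are also the ones whose data are dropped, the adverse event rate falls in whichever arm loses more of them, and a reassuring figure may come partly from selection.

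This matters more here than in most trials of this size. The article describes the first clinical trial of a self-developed device in this disease, self-administered at home. It has no data monitoring committee and no early-stopping procedure ({21a}), and no auditing plan ({23}). The final adverse event table therefore carries most of the safety evidence.

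**Working it through.** **Step 1. Set the sections side by side.**

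| Question | Section | Answer in the text |
|---|---|---|
| Who is analysed for UPDRS III? | {20a} | All randomised |
| Who is analysed for other outcomes? | {20a} | Completers; no other set named |
| Is safety an outcome? | Abstract, {22} | Yes, a primary safety outcome or endpoint |
| What happens to data of those who choose to leave before 4 months? | {18b} | Not kept for analysis |
| May data collected before withdrawal be used? | {19} | Yes, the consent form will permit it |
| Can a serious adverse event end the intervention? | {11b} | Yes |
| Which events are recorded? | {22} | All, from treatment start |
| Whose events are analysed? | {22} | Not stated |

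**Step 2. Follow one participant.** Suppose a participant has a serious adverse event in month 2, stops the device and chooses to leave. The event is recorded under {22}. Under {18b} the participant's data are not kept for analysis. Under {20a}, if safety counts among the other outcomes, the participant is not in the completer set. The event is on file but absent from the result. Section {19} points the other way, because consent covers its use. {18b} and {19} therefore conflict, and {22} does not settle which prevails.

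Now suppose the participant stops the device but attends the 2-month and 4-month visits. {11b} ends the intervention only, and {18b} speaks of participants who choose to leave the study. This participant might still count as a completer, and the event would then be counted. The text does not decide this case.

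**Step 3. Illustrate the size.** The documents give no adverse event rate, so the event counts below are assumptions.

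- Arm size: {14} gives 21 per arm before dropout. 21/0.90 = 23.3, rounded up to 24 per arm, or 48 in total, as the article states. The illustration takes all 24 in the LIPUS arm as treated.
- Assumption: k participants in that arm have a serious event and leave, no one else in the arm has one, and no one else leaves.
- Rate among all treated: k/24. Rate after dropping them: 0/(24 − k).
- Exact (Clopper-Pearson) 95% limits for x events in n: lower = 2.5% quantile of Beta(x, n − x + 1); upper = 97.5% quantile of Beta(x + 1, n − x). For x = 0 the upper limit is 1 − 0.025^(1/n).

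| k | All treated | Exact 95% CI | Leavers dropped | Upper limit |
|---|---|---|---|---|
| 1 | 1/24 = 4.2% | 0.1% to 21.1% | 0/23 = 0% | 14.8% |
| 2 | 2/24 = 8.3% | 1.0% to 27.0% | 0/22 = 0% | 15.4% |
| 3 | 3/24 = 12.5% | 2.7% to 32.4% | 0/21 = 0% | 16.1% |

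For k = 2 the last column is 1 − 0.025^(1/22) = 0.154. The point estimate goes to zero, and the upper limit falls from 27.0% to 15.4%.

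**The case against.** The strongest reply is that no sentence says participants with serious events are left out. It has five parts.

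- **Scope of {20a}.** Its heading covers primary and secondary outcomes, and the outcome lists in {12} do not contain adverse events. Imputation and mean differences, described in the same paragraph, suit scores rather than event counts. On this reading the completer sentence never reached safety. This is the more natural reading, but the wording does not secure it: the Abstract calls safety an outcome, and no other set is named. It also does not answer {18b}, which refers to a participant's data without limiting them to efficacy.
- **The word also in {20a}.** The completer analysis may be an addition to another one. That is possible, but no other analysis of these outcomes is described.
- **Full recording in {22}.** All events are documented from treatment start. This stands as a rule on recording. It does not say whose events are analysed.
- **Treatment versus follow-up.** {11b} ends the intervention, not follow-up, and {18b} asks for every effort to keep patients in until their assessments are done. This stands, and it limits the point.
- **Left to a fuller document.** An article may leave the definition of a safety set to the full protocol or analysis plan. That would answer a complaint about silence. It does not answer stated rules that exclude data and that conflict with {19}.

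The illustration also rests on assumed counts. {11b} reports no adverse events so far during LIPUS treatment. If no one who leaves has an event, the numerator is unaffected.

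**Conclusion.** The concern holds in a limited form. As written, {18b} and {20a} can take early leavers out of the primary safety result, {18b} conflicts with {19}, and both sit badly with {22}. Because a serious adverse event may end treatment and lead a participant to leave, the possible bias is towards lower adverse event rates.

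A reader might infer more: that every participant with a serious event is excluded, so that the serious event rate is near zero by construction. The documents do not support that. The exclusion in {18b} concerns those who choose to leave, {11b} does not end follow-up, and someone who stops the device but attends all visits might still be a completer.

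The size is unknown. If 1 to 3 of 24 treated participants left after serious events, rates of 4.2% to 12.5% would be reported as 0%. This assumes that safety is treated under the {18b} or {20a} rule, that those participants do leave, and that no other serious events occur in the arm.

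**What to change.** Reconcile {11b}, {18b}, {19}, {20a} and {22} on who is analysed for safety, before the analysis is run:

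1. In {20a} or {22}, state that the primary safety endpoint is analysed in every participant who used a device at least once, by device received. Count all recorded events up to the end of the safety window, including those that led to discontinuation or withdrawal.
2. In {20a}, limit the per-protocol sentence to the secondary rating scales, hdEEG and fMRI.
3. In {18b}, remove the exclusion of early leavers' data, or restrict it so that it does not apply to safety data, and bring it into line with the consent provision in {19}.

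The cost is a few sentences of text. No new data are needed, since {22} already has all events recorded. The reported adverse event rates may be less favourable. The change concerns analysis sets only and leaves the clinical rule for ending treatment as it is.

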### Objectives {7}

The aim of the present study is to evaluate the efficacy of LIPUS as a therapeutic intervention for alleviating motor impairments in individuals with PD. In order to achieve the aim of this study, the subsequent research inquiries have been formulated:Is the ultrasound stimulation administered in the LIPUS group more effective than the sham group without ultrasound stimulation in treating movement disorders in PD patients?What cerebral modifications do patients experience as a result of LIPUS therapy?Apart from motor symptoms, are there changes in other symptoms, like depression and anxiety, that may occur?

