## Data collection and management

### Plans for assessment and collection of outcomes {18a}

The primary outcome data will be evaluated at baseline, after 2 months of treatment, and after 4 months of treatment. Secondary outcomes, which encompass additional rating scales and hdEEG, will likewise be assessed at baseline, after 2 months of treatment, and after 4 months of treatment. Furthermore, secondary outcomes, such as fMRI, will be acquired at the baseline and upon completion of the treatment. All variables outlined in the protocol will be meticulously recorded within an encrypted Microsoft Office Excel document. The investigators responsible for data entry in this Office Excel file hold the duty of upholding data accuracy and completeness. To supervise and administer the trial data, a management team has been established, composed of the principal investigator, senior investigator, a research assistant, and a doctorate student each with their respective responsibilities for tasks.

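### The only analysis set stated for the secondary outcomes is completers, so research questions 2 and 3 rest on groups selected after randomisation and later leavers' 2-month data are dropped

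*Protocol article*

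**What the plan says.** Section {20a} of the protocol article names two analysis sets. The first is for the primary outcome: "The intention-to-treat principle will be used to analyze the UPDRS III score (primary outcome"), with all randomised individuals included. The second is for everything else: "A per-protocol analysis of other outcomes from the participants who completed the entire research will also be performed". No section gives MMSE, BDI, BAI, hdEEG or fMRI an analysis in all randomised participants.

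Section {18b} adds a rule that is not limited to any outcome. If a participant leaves during therapy and "fails to complete the entire 4-month treatment duration, their data will not be maintained for the purpose of analysis".

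Three statements point the other way:

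- Section {19}: "The consent form will include permission to utilize data collected prior to the participant’s withdrawal".
- Section {20a}: "Multiple imputations will be used to replace missing data using multivariable regression models with chained equations", with no outcome named.
- Section {20c}, in a paragraph about missing rating-scale assessments, prescribes last observation carried forward (LOCF).

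On timing, {18a} says that the other rating scales and hdEEG "will likewise be assessed at baseline, after 2 months of treatment, and after 4 months of treatment". fMRI is taken only at baseline and at the end of treatment.

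**The concern.** The secondary outcomes answer two of the three research questions in Objectives {7}. The second asks what cerebral changes result from LIPUS, which hdEEG and fMRI address. The third reads "Apart from motor symptoms, are there changes in other symptoms, like depression and anxiety, that may occur", which BDI and BAI address. In a randomised trial both are comparisons between arms.

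Completion is known only after randomisation. If the reasons for leaving differ between arms, completers in the two arms are no longer comparable, and a difference can be created or hidden. Staying on a daily 30-minute home treatment for 4 months could plausibly depend on mood, anxiety or cognition, which these scales measure. That link is a judgement and is not documented in the article.

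Information is also lost. Someone who attends the 2-month visit and stops later has 2-month MMSE, BDI, BAI and hdEEG values that consent allows the trial to use. The primary and secondary results would then describe different sets of people in the same report.

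**Working it through.** **1. The plan's own numbers.** Inputs from {14}: mean changes 5.54 (SD 8.03) and −0.71 (SD 2.25), two-sided alpha 0.05, 90% power, 10% dropout.

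- Difference = 5.54 + 0.71 = 6.25.
- With n per arm, SE = √[(8.03² + 2.25²)/n] = √(69.54/n).
- The unequal-variance t test gives power 0.893 at n = 20 and 0.908 at n = 21, so 21 per arm is reproduced.
- 21/0.90 = 23.3, rounded up to 24 per arm, 48 in total. Reproduced.
- For a 5-point difference at 24 per arm, power is 0.8078. Reproduced.

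The point therefore rests on the wording about analysis sets. No figure in {14} is in dispute.

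**2. The sections side by side, for a participant who attends month 2 and stops in month 3.**

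| Section | Effect on this participant's 2-month scales and hdEEG |
|---|---|
| {18a} | Collected |
| {19} | Consent covers their use |
| {20a}, completer sentence | Participant is outside the set |
| {18b} | Data not kept for analysis |
| {20a} imputation, {20c} LOCF | Fill gaps, but do not say who is in the secondary set |

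Two sections exclude the data, one permits its use, and none assigns the participant to a secondary analysis. fMRI has no 2-month scan, so this loss does not apply to it.

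**3. How many people.** 48 × 0.10 = 4.8, about 5. If completers fall to the 21 per arm in {14}, 48 − 42 = 6. These are ceilings for lost 2-month records, reached only if every leaver attends month 2 first.

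**4. Precision.** The smallest standardised difference detectable with 80% power (normal approximation) is (1.96 + 0.84) × √(2/n):

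- 24 per arm: 2.80 × 0.289 = 0.81 SD.
- 21 per arm: 2.80 × 0.309 = 0.87 SD.

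The loss is small.

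**5. Possible bias.** Let a share p of one arm leave, and let their mean differ by k SD from that arm's completers, with no such selection in the other arm. The mean of the whole arm is (1 − p) × completers' mean + p × leavers' mean. The completers' mean therefore differs from it by p × k, and so does the contrast between arms. The values of k are assumed.

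| p | k = 0.5 | k = 1.0 | k = 1.5 |
|---|---|---|---|
| 0.10 (planned) | 0.05 SD | 0.10 SD | 0.15 SD |
| 0.125 (3 of 24) | 0.06 SD | 0.125 SD | 0.19 SD |
| 0.20 | 0.10 SD | 0.20 SD | 0.30 SD |

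For scale, the standard error of the contrast at 21 per arm is √(2/21) = 0.309 SD. A shift of 0.05 to 0.15 SD is 0.05/0.309 = 0.16 to 0.15/0.309 = 0.49 of a standard error. Equal selection in both arms in the same direction would cancel; selection in opposite directions would add.

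**The case against.** The strongest reply is that the completer analysis will be done in addition to something else, and that {20a} does not say that no other analysis of the secondary outcomes will be run. The section covers primary and secondary outcomes alike, and its imputation sentence is not limited to UPDRS III. {20c} prescribes LOCF for rating scales in general. Imputing for leavers would have little purpose if those scales were analysed only in completers.

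Part of this stands. A reader might infer that the protocol forbids an all-randomised analysis of the secondary outcomes; it does not. What can be said is that completers are the only set stated. Because intention-to-treat is tied by name to UPDRS III, the natural reading is that the completer analysis supplements the primary one. The imputation sentences do not repair this, since they do not say who belongs to the secondary set. If the sponsor intends both analyses, the sentence still needs rewriting.

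Other stronger readings also lack support:

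- **That a tenth of 2-month records will be lost.** This is a ceiling, for the reason given in the working.
- **That brain imaging suffers the same loss.** Only hdEEG does. Even a better fMRI set, everyone with a 4-month scan, remains close to completers.
- **That the bias favours LIPUS.** Nothing in the article fixes its direction.
- **That the shift can be stated in BDI points.** The article gives no BDI standard deviation and no data on leavers.
- **That the per-protocol set ignores adherence.** An adherence threshold may stand in the full protocol or analysis plan, which are not shown.

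It is also fair to say that {18b} conflicts with intention-to-treat for the primary outcome. Settling that conflict would not change the completer sentence for the secondary outcomes.

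**Conclusion.** The point holds in this form: completers are the only analysis set stated for the secondary outcomes, {18b} reinforces this, and {19} shows that consent does not require it. Followed as written, the plan drops usable 2-month scale and hdEEG values and answers research questions 2 and 3 in groups formed after randomisation.

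The size is modest: about 5, at most 6, of 48 participants at the planned dropout. The bias figure of 0.05 to 0.15 SD assumes 10% dropout in one arm, leavers who differ by 0.5 to 1.5 SD, and no such selection in the other arm. It grows in proportion to dropout. The case for change rests on avoidable selection at little cost, not on lost power. It should be corrected, but it does not threaten the primary analysis set, which {20a} defines separately.

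**What to change.** 1. In {20a}, state that MMSE, BDI, BAI and hdEEG will be analysed by randomised group in all randomised participants, using every 2- and 4-month value observed.
2. Name multiple imputation, already in {20a}, as the single main missing-data method. Remove the LOCF sentence from {20c} or keep it only as a sensitivity analysis. Without this step, the two sections still prescribe different methods.
3. Amend {18b} so that data collected before a participant stops are kept for analysis, consistent with {19}. Editing {20a} alone would leave the same records excluded.
4. Analyse fMRI by randomised group in everyone with a 4-month scan, and say plainly that this is still an observed-data set.
5. Keep the completers analysis as a labelled sensitivity analysis.

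The cost is an amendment, which {25} sends to the ethics committee and the register, plus a few more tables. No visits or measurements are added, and the sample size does not change. The downside is that results for leavers will rely on the imputation model. Under {17b} the groups are identified only after the outcome analyses, so a change made before then would not be informed by results by arm.

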**Methods:**

This protocol is a single-site, prospective, double-blind, randomized controlled trial (RCT). Forty-eight participants with clinically confirmed PD will be randomly allocated to one of two groups: LIPUS group or sham group. All of the participants continue to use pharmacological therapy as a fundamental treatment. The primary outcome is the difference between groups from baseline to 4 months in the change in the Unified Parkinson’s Disease Rating Scale (UPDRS) motor score (part III). The secondary outcomes include the rating scales such as the Mini-Mental State Examination (MMSE), and other three rating scales, and medical examinations including high-density electroencephalography (hdEEG) and functional magnetic resonance imaging (fMRI). The primary safety outcome will be assessed at 4 months, and adverse events will be recorded.

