### Outcomes {12}

#### Primary outcome

The primary effectiveness outcome will be the difference in mean change (at baseline, 2 months, and 4 months) across groups (LIPUS vs sham treatment) according to blinded site evaluation of the UPDRS III score for the affected side. The primary outcome is calculated as the sum of the unilateral items for the following: speech, facies, tremor in resting, intentional tremor, rigidity, rapid movements of the fingers, rapid hand movements, alternating movements, leg movements, getting up from a chair, posture, posture stability, starting walking, and bradykinesia in the third section (motor). The scoring system includes the following: 0 points = no involvement; 1 = detectable disorders; 2 = moderate disorders; 3 = considerable disorders; 4 = no function or severe disorders [29]. Therefore, the primary endpoint score ranges from 0 to 56, with higher scores suggesting worse parkinsonism.

Meanwhile, Fahn and Elton created the Unified Parkinson’s Disease Rating Scale (UPDRS), which is made up of six elements. These are as follows: (I) the state of intellectual and mood disorders; (II) activities of daily living (separately for phase “on” and “off”); (III) motor examination; (IV) complications of treatment; (V) stages of the disease; (VI) self-assessment of independence using the Schwab and England Scale. Furthermore, the subjective, patient-derived Activities of Daily Living (Part II) component of the UPDRS corresponds well with the objective, physician-derived motor section (Part III) [30].

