#### Sample size and power {14}

The sample size and power calculations were centered on the primary outcomes, which pertained to the alterations in UPDRS III scores from the baseline assessment to the 4-month follow-up assessment after 4 months of LIPUS treatment. In accordance with the findings derived from the limited sample study involving 20 patients, the LIPUS group exhibited a mean change of 5.54 ± 8.03, while the sham group showed a mean change of − 0.71 ± 2.25. The researcher utilized the sample size calculation software PASS to compute the sample size for each group, which was *n*_1_ = *n*_2_ = 21 (1:1 allocation ratio), to detect differences with a two-sided significance level of 0.05 and 90% power calculations. With the consideration of a 10% dropout rate, the final sample size is expected to be 48. In the prior investigation [36], wherein a clinically meaningful alteration in UPDRS III scores was established as a 5-point disparity, the study determined that the efficiency of the existing sample size in power calculations reached 0.8078.

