## Assignment of interventions: allocation

### Sequence generation {16a}

Participants will undergo randomization, being assigned to either the LIPUS group or the sham group in a 1:1 ratio, facilitated by a computer-generated randomization sequence. To safeguard the impartiality and autonomy of the allocation data, research assistants who are not engaged in outcome assessment will be responsible for generating sequentially numbered opaque sealed envelopes according to the randomization list.

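### The primary UPDRS III comparison is described and sized as a difference in mean change, with no baseline covariate; baseline-adjusted ANCOVA would be a free improvement of small to moderate size

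*Protocol article*

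**What the plan says.** The Protocol article describes the primary comparison in several places, and they agree in form.

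- Primary outcome {12}: "The primary effectiveness outcome will be the difference in mean change". The abstract puts it at 4 months: "The primary outcome is the difference between groups from baseline to 4 months in the change in the Unified Parkinson’s Disease Rating Scale".
- Statistical methods {20a}: "The mean treatment differences and 95% CIs between measures with LIPUS and sham-LIPUS will be computed". No test, model or covariate is named for this comparison. The only regression models in that section serve multiple imputation.
- Sample size {14}: the inputs are raw pilot changes and their SDs. For the active arm, "the LIPUS group exhibited a mean change of 5.54 ± 8.03"; for sham, -0.71 with SD 2.25.
- Data collection {18a}: "The primary outcome data will be evaluated at baseline, after 2 months of treatment, and after 4 months of treatment". Table 1 also schedules UPDRS at the enrolment visit for everyone.
- Sequence generation {16a}: participants are randomised "in a 1:1 ratio, facilitated by a computer-generated randomization sequence". No stratification by baseline score is mentioned.

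**The concern.** A raw change score subtracts the whole baseline value, which fixes the baseline slope at 1. If the true slope of the 4-month score on baseline is below 1, the subtraction is too large, and the arm that happens to start worse will appear to improve more. ANCOVA estimates the slope from the data. With 1:1 allocation and large samples it is never less precise than the change score.

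Two things are at stake. The first is precision at the protocol's own 5-point clinically meaningful difference, where the stated power is 0.8078 with all 24 per arm. The second is that a chance baseline difference in a trial of this size would partly carry through to the estimate, with nothing described in the allocation to limit it. The data needed to deal with both are already being collected.

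**Working it through.** **1. Reproduce the sample size.** Inputs from {14}: changes 5.54 (SD 8.03) and -0.71 (SD 2.25), so the difference is 5.54 + 0.71 = 6.25; two-sided 0.05; 90% power; 10% dropout; 5-point threshold.

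Welch test on change scores, with power from the noncentral t distribution:

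- SE = sqrt((8.03² + 2.25²)/n) = sqrt(69.54/n).
- n = 20 per arm, difference 6.25: power 0.893.
- n = 21 per arm: SE = 1.820, power 0.908. Hence 21 per arm, as stated.
- 21/0.9 = 23.3, rounded up to 24 per arm, 48 in total, as stated.
- n = 24 per arm, difference 5: SE = 1.702, power 0.8078, matching the stated figure to four decimals.
- n = 21 per arm, difference 5: power 0.749.

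The calculation is therefore that of an unadjusted comparison of change scores with unequal variances.

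**2. What adjustment would gain.** The article gives neither a baseline SD nor a baseline to follow-up correlation. Assume a common score SD *s* at both times in both arms. Then the SD of change satisfies SD² = 2s²(1 - r), so r = 1 - SD²/(2s²) in each arm. For s = 8: LIPUS r = 1 - 64.48/128 = 0.50; sham r = 1 - 5.06/128 = 0.96.

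With equal arms, the common ANCOVA slope is the mean of the two, r̄. The summed residual variance is 2s²(1 - r̄²), against 4s²(1 - r̄) for change scores, so the variance ratio is (1 + r̄)/2.

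**3. What a chance imbalance would do.** A one-standard-error baseline imbalance at 24 per arm is s × sqrt(2/24). The part left in the change-score difference is about (1 - r̄) times that.

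| Assumed s | r LIPUS | r sham | r̄ | Variance ratio | SE cut | One-SE imbalance (points) | Shift left in estimate (points) | Adjusted power, 5 points (simulated) |
|---|---|---|---|---|---|---|---|---|
| 6 | 0.10 | 0.93 | 0.52 | 0.759 | 13% | 1.73 | 0.84 | 0.88 |
| 8 | 0.50 | 0.96 | 0.73 | 0.864 | 7% | 2.31 | 0.63 | 0.85 |
| 10 | 0.68 | 0.97 | 0.83 | 0.913 | 4% | 2.89 | 0.50 | 0.83 |
| 12 | 0.78 | 0.98 | 0.88 | 0.940 | 3% | 3.46 | 0.42 | 0.81 |

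The last column comes from simulated trials with 24 per arm, the arm-specific correlations shown, a common-slope ANCOVA and HC3 standard errors. The unadjusted test in the same simulations had power of about 0.80-0.82, and the type I error of the adjusted test was 4.2-4.7%. The closed-form SE cuts are large-sample values. Simulated cuts are slightly smaller: at s = 12 the SE went from 1.71 to 1.68, about 2%.

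**The case against.** The strongest reply is that the protocol never calls the comparison unadjusted. An ANCOVA coefficient is also a mean treatment difference with a confidence interval, a change-score outcome can be analysed with a baseline covariate, and sizing a trial without covariates is common and conservative. Covariates are often left to an analysis plan, which is not shown here. This stands in part. A reader might infer that the protocol commits itself to an unadjusted analysis; the text does not say so, and that reading remains an inference, though a strong one. The outcome definition, the stated estimator and the sample size all describe the same comparison of raw change. The point is therefore a better method for that comparison, and not a complaint about missing detail.

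A reader might also infer that the result would be biased or the test invalid. That is not supported. Under randomisation the difference in mean change is unbiased, its confidence interval already covers chance imbalance, and the planned number meets its stated power. The shift in the table is conditional on an imbalance having occurred, and it needs a slope (r × follow-up SD / baseline SD) below 1, which the article does not let one check.

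Finally, a larger gain is tempting. Taking one correlation of 0.7 or 0.5 in both arms and scaling the pilot SDs gives power of 0.866 or 0.904. But with one correlation, change SDs of 8.03 and 2.25 would need score SDs that differ 8.03/2.25 = 3.6-fold between arms, which randomisation makes implausible at baseline. Those figures should not be relied on.

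**Conclusion.** The point holds as a recommended improvement; it is not an error in a stated figure. As described, the primary comparison does not use the baseline score as a covariate, and it is sized without it.

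The size depends on a baseline SD that the article does not give. Over assumed SDs of 6 to 12, equal at both times and in both arms, adjustment cuts the standard error by about 2-13%. It takes power for 5 points at 24 per arm from about 0.81 to between 0.81 and 0.88. A one-SE chance imbalance would leave 0.42 to 0.84 points in the change-score difference, which is 8% to 17% of the 5-point threshold and a quarter to a half of its SE of 1.70. The gain runs from negligible to several percentage points of power, with no loss in any setting tried.

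**What to change.** In {20a}, before unblinding, state the primary analysis as an ANCOVA of the 4-month UPDRS III score (or, equivalently, its change from baseline) on arm, with the participant's baseline UPDRS III score as covariate. Report the adjusted mean difference with its 95% CI. Use heteroscedasticity-robust standard errors such as HC3, because the pilot SDs differ strongly by arm. Use the same form for MMSE, BDI and BAI with their own baselines. Keep the unadjusted difference in mean change as a supporting result.

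The 4-month score and the change score give the same adjusted treatment difference, so the outcome is unchanged. The cost is a short addition to the analysis section and one degree of freedom, plus the ethics approval and register entry that {25} requires for any modification. No new data, visits or participants are needed. Section {17b} keeps the group identities hidden until the primary and secondary outcomes have been analysed, so the covariate can be fixed blind if that analysis is not yet finished.
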